### Study design

This study is a cluster-randomised, two-arm field experiment conducted in 24 communities in Cape Town (Fig. 1). This cluster design was selected to reduce the likelihood of contamination between study arms.

**Fig. 1 Fig1:**
[figure not shown]
Study Design, with Estimated Recruitment.*An additional 5 clusters are available as replacement communities.**These group sessions occur approximately a week later, which accounts for some attrition.

### Cluster creation and selection

Two geographic areas were selected for the study, one predominantly Coloured (of mixed race ancestry) and the other predominantly Black African. These areas comprise numerous distinct communities that characterise race, population size, area size, and socioeconomic status. Consequently, each community constituted a potential cluster, with large communities subdivided into multiple clusters that yielded 48 clusters across the two geographic areas.

Clusters were selected for inclusion in the study using the following criteria:There must be natural buffers between clusters; for example, at least two streets apart.The predominant race/ethnicity in the cluster must be 90% of the residents or higher.Very small clusters that could not generate the target sample size per cluster were excluded; for example, natural clusters with four or fewer small streets.

Clusters deemed outliers from other clusters were excluded; for example, high socioeconomic status in comparison to similar communities.

### Cluster randomisation

We selected 12 clusters for each of the two geographic areas. Within each block of 12, clusters were randomised to one of the two arms, with equal allocation. Additionally, 5 replacement clusters were selected (3 within the Coloured geographic area and 2 within the Black African geographic area). These replacement clusters will be used if any of the selected clusters are deemed unusable prior to conducting outreach and recruitment in a specific cluster. At times, gangs are very violent, making outreach and recruitment dangerous, even during the day. If this persists in a community, it will need to be replaced for the purposes of this study.

### Study population

Participant eligibility criteria include the following: (1) between 16 and 19 years old; (2) self-identify as a woman; (3) report consuming 2 to 3 alcoholic drinks at least once in the past 30 days *or* using illicit drugs at least once a week in the past 30 days; (4) be currently dropped out of school; (5) have been out of school for at least 6 months; (6) have not completed matriculation (high school) or do not have an N3 (National Technical Certificate) certificate; (7) report condomless sex with a male partner in the past 90 days; (8) report living in one of the 24 target disadvantaged communities; (9) have lived in the target community for at least 6 months; (10) plan to reside in the target community for the next year and can provide verifiable locator information; and (11) provide verbal and written consent. A short cognitive test is given at the end of the eligibility screener [41], and participants are excluded if they do not meet the minimum standard.

### Ethical approval

This study has been approved by the RTI International Committee for Protection of Human Subjects in the United States and the South African Medical Research Council’s (SAMRC) Ethics Committee in South Africa. All participants are required to provide informed consent prior to participating in the study. In the case of 16- to 17-year-old participants, assent is required, in addition to permission for consent by an older female community member who serves in loco parentis (in place of the parent). This approach has been used successfully in our previous South African study with adolescents (Carney et al.: Adolescent female school dropouts who use drugs and engage in risky sex: a brief pilot trial in South Africa, under review). Because of the sensitive nature of this study, in loco parentis enables the participant to select a female adult (either identified by the participant themselves or by the project staff), other than a parent, to provide consent on her behalf. This practise is used because if parents learn about a participant’s AOD use and sexual activity, it could result in conflict or violence in the family.

Once an older woman who will provide consent in loco parentis is identified, project staff schedule an appointment for the potential participant and the adult woman to conduct the consent process and provide written consent acting in loco parentis. Both the potential participant and her designated adult sit together during the initial consenting process. Following that, the potential participant is screened separately to confirm eligibility again, and she is assented separately from the adult woman to prevent coercion and to maintain confidentiality about sexual risk and AOD use. Any adult woman acting in loco parentis is also required to sign a confidentiality agreement form as part of the consent process so they understand that their experience at the project site is also confidential and that they must maintain confidentiality.

### Data and safety monitoring plan and data and safety monitoring board

This study utilises a Data and Safety Monitoring Plan (DSMP) to ensure the utmost protection of participants and their privacy. The DSMP includes a day-to-day procedural manual comprising data management and monitoring guidelines for project staff. Study data are kept confidential in a secure location, and identifiable information is stored separately from information with the participant’s alphanumeric study identification code (participant ID). All project staff are required to sign a confidentiality agreement, and they receive training on ethical roles and responsibilities in maintaining the privacy of participants. Procedures are in place to handle adverse events (AEs) or serious adverse events (SAEs), such as improper disclosure of information or mental or emotional discomfort. The study also utilises a Data and Safety Monitoring Board (DSMB) comprising three members: an expert in adolescent health, an infectious disease epidemiologist, and a bioethicist clinician. The DSMB meets every 6 months to review study progress and ensure adherence to the DSMP.

### Study procedures

#### Recruitment

The study uses female adolescent peer role models (aged 18 to 25) called Expanded Public Works Programme (EPWP) beneficiaries in combination with trained outreach workers to assist in reaching and recruiting participants. The peer EPWP beneficiaries are selected each year with help from the Western Cape Department of Social Development. They are trained on a series of topics, including professionalism, job expectations, AOD use, gender awareness, and community engagement. The EPWP beneficiaries also receive certification in a simplified Collaborative Institutional Training Initiative (CITI) training for human subjects and obtain training on completing daily outreach reports. Trained study outreach workers—who have worked in and around the target communities and are familiar with community outreach methods—offer oversight to the EPWP beneficiaries. The purpose of this team effort is to reach adolescent women who have dropped out of school and are using AODs. The trained study outreach workers conduct the screening with adolescents who they have identified during outreach, or the EPWP beneficiaries have referred them to, to ensure privacy and confidentiality. Study staff are multilingual in English and Afrikaans and/or isiXhosa.

Outreach is conducted in areas of high target population density in the selected communities. Trained EPWP beneficiaries and study staff post recruitment cards and fliers in their targeted communities, paying special attention to establishments where adolescent women who are out of school are known to frequent, such as community centres or libraries. Marketing about the study is conducted by walking through the neighbourhoods looking for adolescent women who may be hanging out near tuck shops (small, food-selling vendors), corners, and hair and nail salons; and by talking with community members. Potential participants who either contact project staff using the numbers given on the recruitment cards and fliers or who are approached through outreach are screened for eligibility by study staff.

#### Intake assessment

Participants are transported to a secure field site for all study activities. After final eligibility is determined through a rescreening, consent and/or assent is obtained, participants take a breathalyser test for recent alcohol use, locator information is collected, and a photograph of the participant is taken (which is returned at the final appointment). At this first appointment, participants complete the baseline questionnaire via computer-assisted personal-interviewing (CAPI) technology, and audio computer-assisted self-interviewing (ACASI) in their home language (English, Afrikaans, or isiXhosa) for sensitive topics, such as experiences of abuse. Staff then collect biological specimens to conduct pregnancy testing, screening for recent drug use, and rapid HIV testing. A urine specimen sample is collected to perform rapid tests to detect metabolites of recent use of cocaine, methamphetamines, amphetamines, opioids, ecstasy, and marijuana via a 5-panel drug screening test. Methaqualone (Mandrax) is measured through a separate urinalysis test. Two rapid tests are conducted for HIV testing; if a participant has a positive test result for either test, she receives a third test and posttest counselling in accordance with the national South African standards. If two tests show a positive HIV result, the participant is considered to have a positive test. All staff undergo training for biological specimen collection and are certified to conduct rapid HCT. All positive HIV screening determinations or positive test results for pregnancy are referred to the local health clinic regardless of study arm. For other services needed, participants in the intervention arm receive active referrals, whereas participants in the HCT control arm receive passive referrals.

#### Modifications to the protocol

We modified the protocol to improve the study design and to implement follow-up study procedures. Table 1 summarises these amendments, all of which were approved by the appropriate ethical boards. Each modification is explained in the table.

**Table 1 Tab1:** Modifications to the Study Protocol

Date of Approval	Modification
August 2016	Reduced incentive amounts. Participants who have two positive (reactive) test results for their screening tests will not undergo a third (confirmatory) test. Increased the number of clusters from 12 to 24. Revised the screener, consent forms, and questionnaire to reflect protocol changes and the supplemental forms to reflect feedback during instrumentation programming and testing.
October 2016	Young women who cannot sign their signature or do not have a signature, will be asked to provide an inked fingerprint in place of a signature in accordance with South African Good Clinical Practice (GCP) guidelines. The alcohol breathalyser test was moved to the beginning of the intake appointment to have a valid assessment of alcohol use. Case management will consist of calls or in-person check-ins. Revised the consent form and locator form to reflect changes regarding case management and the baseline questionnaire and significant individual contact form based on instrument programming and testing.
April 2017	Addition of 6-month follow-up protocol: Submission of the 6-month follow-up consent form and 6- and-12-month questionnaire.
October 2017	Addition of 12-month follow-up protocol: Submission of the 12-month follow-up consent form. Updated all previously approved consent forms and the Rights of Research Participants Card to reflect change in chairperson.
November 2017	Made a minor change to the 12-month follow-up consent form. Edited the ACASI section of the baseline and follow-up instruments, which included adding referral prompts related to self-reported violence experienced in the past 3 months.

### Study activities by arm

#### Intervention arm

Participants in the intervention arm take part in all of the activities described above for the control arm. Additionally, they are asked to attend two group workshops of the YWHC. Participants are contacted by staff to confirm attendance to the intervention workshops within a week of their intake appointment. Up to eight participants form a workshop group.

The intervention consists of two group workshops lasting approximately 2 h each, with each workshop containing several modules and exercises (see Table 2 for a detailed summary of the workshop content). Workshops are conducted approximately 7 to 10 days apart. Workshop 1 covers developmental issues, AODs, pregnancy and parenting, gender issues, violence, communication, and negotiation. Workshop 2 covers sex and risk, HIV and other STIs, sexual risk reduction (including male and female condoms), and safer sex negotiation with partners. The modules include voices and quotes from the formative focus group discussion participants who willingly shared their stories. Both workshops end with each participant working toward developing a personalised risk-reduction action plan. As with the intake, active referrals are offered where appropriate.

**Table 2 Tab2:** Young Women’s Health CoOp Workshop Content

Workshop 1		
Topic	Slides	Activity
Becoming a Woman	• Life Stages of Development • Who Influences You • Growing up and Maturing • How Can You Be in Control? • Becoming Your Own Woman • Making Decisions and Never Too Late to Change	
Alcohol and Other Drug (AOD) Use	• AOD Use Compromises Young Women • Intersecting Risks • Using Alcohol and Other Drugs • Types of AODs and Risks • Effect of AOD Use on Sex • Risks of Using AODs • Reducing AOD Risks	Drug Type Activity
Pregnancy and Parenting	• Breastfeeding • Teen Parenting Challenges • Tips for Being a Good Parent	
Communication and Negotiation	• Learning How to Communicate and Negotiate With Others • Understanding Conflict • Conflict Resolution Steps • Ground Rules for Conflict Resolution	Conflict Resolution Role-play
Gender and Power	• Inequality and Lack of Power • Types of Boyfriends • Getting Away from Bad Boyfriends • Gangs and Issues • When Things Go Wrong • Response to Danger with Guys	
Violence	• Intersecting Risks • Rape and Sexual Assault • Truths and Myths of Rape • Safety Tips When Going Out	Truths and Myths of Rape
Behaviour Change	• Resources for Change • Identifying Support and Healthy Role Models • Dreams and Goals	
Personalised Action Plan	• Reduce AOD use • Conflict Resolution and Violence Prevention • Improve Life Situation	Complete Workshop 1 Goals and Steps in Booklet
Workshop 2		
Topic	Slides	Activity
HIV	• Why Reaching Young Women Is Important • What You Need to Know • How Do Young Women Get Infected with HIV? • What Is HIV? • What Young Women Say about HIV Testing • Window Period • If Someone Is Infected with HIV • Breastfeeding and HIV	
Sex and Risk	• Intersecting Risks • Levels of Sexual Risk • Relationships and Expectations • Sexual Pressure • Unprotected Sex	Sexual Risk Activity
Male and Female Anatomy	• Examining Body Parts • Keeping Private Parts Healthy • Male Anatomy	
STIs	• STI Facts • Types of STIs • How to Get Help • Preventing HIV and Other STIs	Treatable versus Curable STIs
Male and Female Condoms and Protection	• Male Condom and How to Use It • Female Condom and How to Use It	Male and Female Condom Demonstration and Practise
Other Sexual Activities and Risks	• Oral Sex and Clingwrap/Oral Dams • Exchanging Sex • Reducing Sex Risks • How to Stay Healthy	
Safer Sex Negotiation	• Being Strong, Safe, and Healthy Young Women • Tips for Effective Refusal for Not Having Sex • How to Talk With “The Guy” About Safer Sex • Negotiating with Different Partner Types	
Personalised Action Plan	• Protect Health • Improve Life Situation	Complete Workshop 2 Goals and Steps in Booklet

#### Control arm

Participants in the control arm receive the standard HCT protocol performed in South Africa, as mentioned in the intake assessment. Additionally, participants obtain referrals upon request to other health services, except in the case of pregnancy or HIV-positive screening determination.

### Participant satisfaction forms

When participants complete the intervention, they are asked to reflect on their experience by completing a Participant Satisfaction Form by themselves. This information provides feedback on how effective the YWHC was for each participant who completed both workshops. The form asks questions about what the participant learned, the changes they made, and for suggestions regarding the aspects of the intervention they would change or improve. The form also asks about the usefulness of the personalised action plan in helping participants improve their life and if they would encourage others to attend the workshops.

### Case management of personalised action plan goals

After completion of the second workshop, staff follow up with participants individually to assist them with attaining the goals developed in their personalised action plan. Staff check in approximately monthly via mobile phone or in person. Because a majority of participants do not have mobile phones, most of the case management is conducted in person.

### Fidelity of the intervention

The fidelity of the intervention workshops is assessed by audio-recording the workshops, with the consent/assent of all participants. The South African Project Director or designee listens to all of the recordings and provides feedback to the interventionists in the following areas: (1) coverage of all the activities that should be included in the two workshops, which is an assessment of whether the interventionist covers all the relevant topics, conducts all the activities, and ensures that the skills are practised by participants; and (2) delivery of the workshop to ensure that the interventionist covers the material on the curriculum, maintains focus during the group workshop, and monitors time to ensure that the workshop is not too lengthy. The assessment also includes the style in which the interventionist provides the workshop; for example, if she was nonjudgmental in her approach, asked participants questions, and could answer the questions. The South African Project Director also checks whether the personalised action plans are completed by each participant that attends the workshops, and whether the goals are concrete and measurable.

### Follow-up assessment

Participants in both study arms return for 6- and 12-month follow-up assessment, which includes reconsenting, updating locator information, administering a follow-up questionnaire, and biological testing. Each of these two appointments lasts approximately 1.5 h. If a participant tests positive for HIV at baseline, they are not tested again for HIV at follow-up.

### Outcome measures

The primary outcomes of this study are reduced AOD use (as measured by AOD testing and by self-reported frequency of AOD use) and reduced sexual risk (as measured by condomless sex, self-reported number of casual partners, sex trading, and partner concurrency) in the past 30 days. We used the Revised Risk Behavior Assessment (RRBA) with youth measures to assess these outcomes. An additional outcome is reduced violence and victimisation in the last 3 months [42].

The secondary outcomes of this study include access to health services, as measured by self-reported use of sexual reproductive health services and HIV and STI testing services, linkage to HIV treatment and care services, and staging and antiretroviral therapy (ART) initiation, and advancement as it pertains to education and job training, as measured by enrollment in training certifications, self-reported motivation and perception regarding learning, and self-reported knowledge regarding strategies to improve educational outcomes.

### Staff training

The intervention facilitators, including the EPWPs, are trained by the Principal Investigator or the South African Project Director on the intervention workshops. All project staff involved are trained on the research methods, data collection, and issues surrounding confidentiality. Further, all field staff receive a field manual and training on safety and security procedures, protection of human subjects, and how to conduct active and passive referrals.

### Data management and quality assurance

To protect participants’ confidentiality, several procedures are implemented at both the field site in South Africa and at RTI headquarters in the United States. All study participants receive a computer-generated participant ID that is used on all study-related data in paper and electronic form. The participant ID contains a check digit and all data collection software verifies that only valid participant IDs are entered. Project files and databases associated with this study are only available to research personnel through the authorisation of the project’s Principal Investigator. All locator information is stored in double-locked cabinets in the field site location.

CAPI and ACASI are used for the personal data collection, allowing for checking errors in real time. ACASI provides the privacy for collecting more sensitive data and the advantage of having the interviewer offer to assist with question comprehension. Data management is conducted by RTI’s Research Computing Division. Data are transmitted daily to RTI and processed nightly, with reports sent to project team members. An edit report identifies data issues needing attention, a tracker report displays key information from data records for each participant, and a production report prints needed statistics to evaluate study progress.

Biological data are collected for pregnancy, AOD use, and HIV through urinalysis, breath scans, and blood specimen collection. There is no storage of biological specimens because they are immediately disposed of as medical hazard waste following testing.

### Adverse events and severe adverse events

If participants experience AEs or SAEs in direct relation to any aspects of the study, the South African Project Director will complete an Incident Report immediately and contact the South African Co-Investigator and the Principal Investigator for additional guidance, as needed. The field staff will make appropriate referrals to medical, counselling and/or other health services. SAE and Incident Reports will be reviewed by the Principal Investigator as soon as they occur. SAEs, such as death or hospitalisation, will be reported within 24 h of their occurrence by the Principal Investigator to the National Institute on Drug Abuse Project Officer, RTI’s Office of Research Protection, the SAMRC Ethics Committee, and the DSMB described earlier.

### Sample size and power

#### Power considerations for Aim 2

This study proposes several primary outcomes for Aim 2, and the power analysis were conducted to ensure that the study was adequately powered to detect intervention effects on these key outcomes, such as proportion of condom use (see earlier description of primary and secondary outcomes). The assumptions for this analysis are based on past studies of the WHC in South Africa and the Young Women’s CoOp pilot efficacy study conducted in the United States. In past studies, the proportion of condom use has ranged from 0.3 to 0.6. For all power analysis, we assumed a two-sided test with α = 0.05, a power of 0.8, and an intracluster correlation coefficient (ICC) estimate of 0.01. Based on these parameters, with a sample size of 225 per intervention arm at 12-month follow-up (an expected 90% follow-up) and 24 clusters, the minimal detectable difference is 0.13 for the outcome of condom use at the highest proportion of 0.6. For outcomes that may be less common overall, such as biologically confirmed HIV, we will be able to detect similar differences, ranging from 0.10 to 0.13.

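### The power section quotes a detectable difference of 0.10 to 0.13 for biologically confirmed HIV without a control risk; that range fits outcomes affecting about 19–36% of controls, not 12-month new infections unless incidence is very high

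*Protocol article*

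**What the plan says.** The protocol article, under Sample size and power (Power considerations for Aim 2), states its inputs: "we assumed a two-sided test with α = 0.05, a power of 0.8", with "an intracluster correlation coefficient (ICC) estimate of 0.01" and "with a sample size of 225 per intervention arm at 12-month follow-up (an expected 90% follow-up) and 24 clusters". It reports that condom use ranged from 0.3 to 0.6 in past studies and concludes that "the minimal detectable difference is 0.13 for the outcome of condom use at the highest proportion of 0.6". It gives no figure for the rest of that range.

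For less common outcomes, "such as biologically confirmed HIV, we will be able to detect similar differences, ranging from 0.10 to 0.13". No HIV incidence or control-arm HIV risk appears anywhere in the article.

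The Follow-up assessment section states: "If a participant tests positive for HIV at baseline, they are not tested again for HIV at follow-up".

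HIV infection is not a primary or secondary outcome in Objectives or Outcome measures. The HIV-related outcomes there concern testing, linkage to care and treatment initiation.

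**The concern.** A detectable difference means little without the control proportion it belongs to. For a rare event, the whole control risk may be smaller than the difference quoted. Infection status at entry is fixed and, under randomisation, has the same expectation in both arms, so any effect of the intervention on HIV must come from infections acquired during the 12 months. A sentence offering 0.10 to 0.13 for that endpoint tells the reader that HIV is covered by the power calculation, when the figure may exceed anything the intervention could achieve.

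HIV prevention is the stated motivation of the trial. If seroconversions are reported later and do not differ between arms, the published sentence invites the reading that the trial was adequately powered and the intervention did not work.

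**Working it through.** **Inputs, from the power section and Cluster randomisation:** 225 analysed per arm at 12 months; 24 clusters allocated equally, so 12 per arm; ICC 0.01; two-sided α = 0.05; power 0.80.

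**Effective sample size.** Mean cluster size m = 225/12 = 18.75. Design effect = 1 + (18.75 − 1) × 0.01 = 1.1775. Effective n = 225/1.1775 = 191.1 per arm.

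**Formula.** The smallest detectable difference d solves d = (1.960 + 0.842) × √{[p0(1 − p0) + p1(1 − p1)]/191.1}, where p1 = p0 + d for an increase and p0 − d for a reduction. Power for a given pair is Φ(|p0 − p1|/SE − 1.960), where SE is the square-root term.

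**The plan's own figure.** For an increase from 0.6, d = 0.134 (0.135 with pooled variance), which rounds to the stated 0.13. The figure reproduces.

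**Where 0.10 to 0.13 comes from.** For a reduction, d = 0.10 when p0 is about 0.19 and d = 0.13 when p0 is about 0.36 (0.193 and 0.358 with pooled variance; 0.195 and 0.365 unpooled). The quoted range is thus correct for moderately common outcomes.

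**HIV: the floor on control risk.** A risk cannot fall by more than its own size. A reduction of 0.10 to 0.13 needs a 12-month control risk of at least 0.10 to 0.13, even with complete prevention. That is a share of all controls analysed; among those negative at baseline it would have to be higher.

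**HIV: what the design gives at lower risks.** The control risks below are assumptions. All 225 per arm are kept, which is generous because baseline positives cannot seroconvert.

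| Assumed control risk | Smallest detectable reduction | Power for a halving | Power for complete elimination |
|---|---|---|---|
| 0.02 | none | 12% | 50% |
| 0.03 | none | 17% | 68% |
| 0.05 | 0.046 (a 92% reduction) | 25% | 88–89% |
| 0.10 | 0.070 | 46% | over 99% |

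Example at 0.05 halved to 0.025: SE = √[(0.0475 + 0.0244)/191.1] = 0.0194; 0.025/0.0194 = 1.29; Φ(1.29 − 1.96) = 0.25. Example at 0.03 eliminated: SE = √(0.0291/191.1) = 0.0123; 0.03/0.0123 = 2.43; Φ(2.43 − 1.96) = 0.68. If only 80% were negative at baseline (also an assumption), power for a halving would be about 11%, 21% and 39% at 0.02, 0.05 and 0.10. The normal approximation is rough with so few events, so these are orders of magnitude.

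**Condom use across the stated range**, for an increase, the intended direction:

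| Control proportion | Detectable increase | Power for a true 0.13 |
|---|---|---|
| 0.30 | 0.137 | 76% |
| 0.43 (peak) | 0.142 | 73% |
| 0.50 | 0.140 | 73% |
| 0.60 | 0.134 | 78% |

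The value at 0.6 is the smallest in the range. None of these figures credits baseline adjustment.

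**The case against.** A reader might infer that the design cannot detect a difference of 0.10 to 0.13 in HIV, or that about 20% control risk is needed to reach 80% power for it. Neither is right. The absolute detectable difference shrinks as outcomes become rarer: power for a reduction of 0.10 is about 0.97 from 0.12 to 0.02, 0.91 from 0.15 to 0.05, and falls to 0.79 from 0.20 to 0.10. If so large a drop occurred from a low base, the trial would find it. The trouble is that the quoted effect may be unattainable, not that it is undetectable.

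It can also be said that HIV is only an example in that sentence, that neither Outcome measures nor the Analysis section plans a test on HIV infection, and that the implausibility depends on an incidence the document does not give. All three stand, and they limit the weight of the point. They do not rescue the sentence, which makes a positive power statement for a named endpoint without the one number that would give it meaning.

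On condom use, the stated figure reproduces and the article says openly that it applies at 0.6. The shortfall elsewhere in the range is 0.003 to 0.008. The Analysis section adjusts for the baseline outcome; if the baseline–outcome correlation were 0.3 (an assumption), every value would be multiplied by √(1 − 0.09) = 0.954, giving 0.128 to 0.135. It would therefore be too strong to say that power is far below 80%.

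It is also tempting to argue that 0.6 is an unlikely starting value because entry requires women to "report condomless sex with a male partner in the past 90 days". That does not follow. The criterion asks for any such episode in 90 days before enrolment, the outcome covers 30 days at follow-up, and the entry criteria of the past studies are not shown. A t reference with 22 degrees of freedom would raise the detectable increases to about 0.140 to 0.148, but that choice commonly belongs in the analysis plan and is not an error here.

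**Conclusion.** The HIV part of the power sentence is wrongly stated. The range 0.10 to 0.13 is correct for reductions from control proportions of about 0.19 to 0.36. Applied to new infections over 12 months, it presupposes that at least 10–13% of controls seroconvert, and the article neither states nor supports such a risk. At assumed control risks of 2%, 5% and 10%, power for a halving is about 12%, 25% and 46%; at 3%, even complete elimination has about 68% power.

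The floor of 10–13% follows from the document alone. The power figures for a halving or elimination depend on the assumed risks and on the plan's ICC of 0.01. The point concerns how a property of the design is reported; it does not show that the trial is too small for its listed outcomes. The condom-use part is a minor matter of reporting: about 0.13 to 0.14 across the range, not 0.13 at its most favourable end.

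**What to change.** Remove HIV from the power sentence and say instead that reductions of about 0.10 to 0.13 are detectable for outcomes with control proportions of about 0.19 to 0.36. Alternatively, keep HIV, state the assumed 12-month control risk and the number at risk, and give the matching detectable difference. In either case, report any seroconversions by arm with a confidence interval and make no claim of adequate power for them.

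As a small addition, give the detectable increase in condom use across the whole 0.3 to 0.6 range (0.137 at 0.3, a peak of 0.142, 0.134 at 0.6), noted as before any gain from baseline adjustment.

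The cost is a few words of text and a slightly less favourable stated figure. Enrolment, the number of clusters and follow-up are unchanged.
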